### Body Composition and Cachexia

Body mass and composition analyses will be performed using a bioelectrical impedance meter (SECA mBCA 515, SECA, Hamburg, Germany), validated in comparison to different robust methods assessing body composition, such as air-displacement plethysmography, dual-energy X-ray absorptiometry, and deuterium dilution (55). The bioelectrical impedance meter is also regularly used in studies investigating body composition in cancer patients (56–59). We will quantify body mass, fat free mass, fat mass, skeletal muscle mass, visceral fat, and body water repartition. Patient height will be measured to calculate body mass index (BMI, body mass/height^2^).

In accordance with Fearon et al. (4), cachexia will be diagnosed using fat-free mass index cut-off (i.e., <14.6 kg/m^2^ for men and <11.4 kg/m^2^ for women) assessed by a bioelectrical impedance meter (4). Furthermore, the severity of the cancer-related body mass loss (i.e., cachexia) will be investigated using the Martin score (28) at the second and third visit. Martin score is a robust grading system incorporating the independent prognostic significance of both BMI and percentage of body mass loss based on a correlation matrix from a cohort of more than 8,000 cancer patients (28). A severity stage of body mass loss between 0 and 4 is attributed to each patient according to their BMI at cancer diagnosis (28), with stage 0 being the lowest severity stage of cachexia, and stage 4, the highest. Importantly, each score is associated with a specific cumulative survival curve: the lower the score, the greater the survival probability (28).

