### Sample Size

An *a priori* sample size estimation was performed using the following sample size calculation formula (68):

$$\begin{array}{l} Sample\;size\;=\;\frac{{Z_{-a/2}}^{2}SD^{2}}{d^{2}} \end{array}$$

Where: *Z*_−*a*/2_ is a standard normal variate (at 5% type 1 error i.e., *P* < 0.05, it is 1.96); *SD* is the standard deviation of the main variable based on previous study; and *d* is the absolute error or precision based on previous study.

The primary outcome of this study is to investigate the evolution of exercise tolerance using the 6-MWT distance. According to Granger et al. (69), a 9.5% decline in the walking distance (i.e., exercise performance) during the 6-MWT test is sufficient to show a clinical decrease in exercise tolerance. Thus, based on the evolution of 6-MWT distances between the first and the second visit in our study, the hypothesis was that cancer patients will reduce, by at least 9.5%, their 6-MWT performance, and thus exhibit signs of exercise intolerance. We also determined the expected baseline 6-MWT results (659 ± 62 m) from the results observed in a healthy subjects group aged 55–75 years old (70), and a 7-m precision was calculated according to a test-retest reliability performed by Demers et al. (67). Using an α level of 0.05 and a power (1-β) of 0.95, the total sample size was calculated as follows:

$$\begin{array}{l} Sample\;size=\frac{1.96^{2}{\left(62\right)}^{2}}{7^{2}}=301 \end{array}$$

Our sample (*n* = 301) will be equally divided into our three groups of interest: 100 lung cancer patients, 100 breast cancer patients, and 100 colorectal cancer patients.

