### Statistical Analysis

Normality and variance homogeneity will be investigated on all collected data using the Shapiro-Wilk test and the Levene test, respectively. Appropriate parametric or non-parametric analyses will then be performed. Statistical significance will be set at *P* < 0.05. All values will be expressed as mean ± standard deviation or median ± range.

A multivariate analysis of variance (MANOVA) will be used on our primary outcome (i.e., exercise tolerance) and secondary outcomes (i.e., quality of life, fatigue, physical activity level, strength, fatigability, body composition, cachexia, physical performance, and respiratory function) to protect against Type I errors arising from multiple comparisons. A two-way mixed-design ANOVA will be used (group [lung cancer – colorectal cancer – breast cancer] × time [first visit – second visit – third visit]). Finally, if a significant difference is found, a multiple-comparison analysis will be performed using an appropriate *post-hoc* test.

Finally, interaction between specific variables will be tested with Pearson's correlation coefficients (*r*^2^). For example, we plan to test the possible correlation between subjective and objective fatigue, or between exercise tolerance/quality of life and body composition.

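### The MANOVA does not give the Type I error protection claimed for the secondary outcomes, and cachexia severity does not fit a three-visit normal-theory model

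*Protocol article*

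**What the plan says.** The Statistical Analysis section of the protocol article states: "A multivariate analysis of variance (MANOVA) will be used on our primary outcome (i.e., exercise tolerance) and secondary outcomes". The secondary domains listed are quality of life, fatigue, physical activity, strength, fatigability, body composition, cachexia, physical performance and respiratory function. The stated purpose is "to protect against Type I errors arising from multiple comparisons". A group-by-time mixed ANOVA over three visits follows, then an unnamed post-hoc test if something is significant. One level covers everything: "Statistical significance will be set at *P* < 0.05". No rule makes the ANOVAs depend on the MANOVA result, and no adjusted level or order of testing is given.

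The Sample Size section names one primary outcome, 6-MWT distance, and hypothesises a fall of at least 9.5% between the first and second visits.

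The Body Composition and Cachexia section defines cachexia in two ways: a yes/no cut-off on fat-free mass index, and a severity stage from 0 to 4 scored "at the second and third visit". The cachexia row of Table 2 likewise has no mark at Visit 1.

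**The concern.** The protocol gives the MANOVA a specific job, control of Type I error over many outcomes, and the method does not do that job in the situation the protocol expects. An omnibus test guards the follow-up tests only under the global null. Once one outcome truly changes, a significant MANOVA is the expected result, and it says nothing about which of the other outcomes changed. Each of those is then tested at 5% with no adjustment.

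The Discussion intends to use the pattern of changes by cancer type to choose exercise interventions for later trials. False positives among the secondaries would feed directly into that choice, under a stated assurance that multiplicity had been handled.

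Two further points follow. A single pre-specified primary test needs no multiplicity protection, so placing the 6-MWT in the omnibus test gains nothing. And one listed outcome, cachexia severity, has neither the scale nor the visits that the analysis requires.

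**Working it through.** **The plan's own figure.** The protocol gives no error rate for the MANOVA procedure. The figure it does give, the sample size, reproduces: 1.96² × 62² / 7² = 301.4, stated as 301 and run as 3 × 100. That supplies the SD (62 m) and the group sizes used below.

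**How many outcomes.** The Statistical Analysis section lists ten domains. Counting every score named under the assessment headings gives 6-MWT 1, QLQ-C30 15, FACIT-F 3, GPAQ 1, force 2, fatigability 2, body composition 7 (six plus BMI), cachexia 2, SPPB components 3, spirometry 10: a total of 46. The protocol does not say which scores enter, so 10 and 46 are taken as the two ends.

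**Does the omnibus test become significant under the protocol's own hypothesis?** The expected fall is 0.095 × 659 = 62.6 m. Taking the reported test reproducibility of 0.85 as the between-visit correlation (an assumption), the SD of change is 62 × √(2 × 0.15) = 34 m. For Hotelling's T² on the Visit 1 to 2 change, the noncentrality is n(δ/SD)² = 300 × (62.6/34)² ≈ 1,017. Power is about 1.00 with 1, 10 or 46 outcomes. It is still about 1.00 with an SD of change of 62 m and n = 200. So the MANOVA is expected to be significant on time.

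**What happens to the other outcomes.** The check simulated three groups of 100, one score per outcome, a Pillai MANOVA, then one-way ANOVAs at 0.05, with 1,500 runs per setting. The common correlation between outcomes is assumed. One outcome is truly different by 1 SD in one group, and ANOVAs count only if the MANOVA is significant. The MANOVA was significant in 95–100% of runs. The chance of at least one false positive among the remaining outcomes was:

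| Correlation | 10 outcomes | 46 outcomes |
|---|---|---|
| 0 | 0.37 | 0.86 |
| 0.3 | 0.34 | 0.76 |
| 0.5 | 0.26 | 0.59 |
| 0.8 | 0.17 | 0.29 |

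As a check on the first row, nine independent tests give 1 − 0.95⁹ = 0.37. With a smaller true difference (0.4 SD) the MANOVA is significant less often, and the risk is 0.17–0.25 for 10 outcomes and 0.17–0.27 for 46. These figures cover one effect per outcome; a mixed ANOVA tests three.

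**Where the protection does hold.** With no true effect and the ANOVAs conditional on the MANOVA, the familywise error is about 0.02–0.06. If the ANOVAs are not conditional, and the protocol does not say that they are, it is 0.18–0.43 for 10 outcomes and 0.29–0.92 for 46, even with no true effect.

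**Cachexia severity.** The stage is ordinal with five levels, and exists at two visits. The time factor has three levels. With severity included, no patient has a complete three-visit record. The yes/no cut-off could be derived at Visit 1, because body composition is measured there, but it is binary and equally unsuited to a normal-theory model.

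**The case against.** The strongest reply is that this is a descriptive cohort with one primary outcome, so an overclaimed rationale for the secondaries is a matter of wording. That bears on how serious the point is and is accepted. It does not remove the point, because the claim of protection is explicit and is not something left to a fuller document.

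Four stronger readings are tempting, and the documents do not support them.

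- A reader might infer a 90% false-positive risk, from 1 − 0.95⁴⁵. That needs all 45 other scores to be tested and to be independent. The list gives only domains, and overlapping lung-function, body-composition and quality-of-life scores are unlikely to be independent.
- A reader might infer that the whole model cannot be fitted, because body mass is the sum of fat and fat-free mass. The article says of its measurements: "We will quantify body mass, fat free mass, fat mass, skeletal muscle mass, visceral fat, and body water repartition". That is what is measured, whereas the MANOVA list says only body composition. Singularity arises only if a total enters with all its parts. The three-visit factor is also attached to the mixed ANOVA, and the MANOVA's own design is not given.
- A reader might infer that the primary test is compromised. No dependence of the 6-MWT ANOVA on the MANOVA is stated. If there were one, power at 62.6 m would still be about 1.00. Loss appears only for smaller effects: for a 7 m change (SD of change 34 m, n = 300), 0.95 alone against 0.66 with 10 outcomes and 0.30 with 46; for a 0.4 SD group difference, about 0.83 against 0.16–0.74 with 46.
- A reader might infer that deletion of incomplete records would empty the cohort. The article gives neither a missing-data rate nor a method, and its silence on this is no finding.

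The article's sentence about choosing parametric or non-parametric methods does not rescue either remaining point: it supplies no multiplicity adjustment and no Visit 1 severity stage.

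**Conclusion.** The point holds in two parts. First, the stated Type I error protection is absent for the secondary outcomes once any outcome truly changes, which is what the protocol expects of its primary outcome. With one large true effect, the risk of at least one false positive among the others is about 0.17–0.37 on the most favourable count of ten scores and about 0.29–0.86 on the full count of about 46, against the implied 0.05. The ranges rest on assumed correlations of 0.8 down to 0, on a simplified one-way layout, and on follow-up tests at an unadjusted 5%. The conclusion does not depend on which count is right. Second, cachexia severity cannot be analysed as listed over three visits.

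The primary 6-MWT comparison is not endangered at the design effect, so this should be fixed but is not critical to the study's main result.

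**What to change.** Remove the MANOVA as the error-control device and state instead:

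- The Visit 1 to Visit 2 change in 6-MWT distance, the hypothesis in the Sample Size section, is tested on its own at two-sided 5%.
- Each secondary outcome is analysed in its own model. A short named list is controlled by Holm or a false-discovery-rate procedure; all others are reported as exploratory estimates with confidence intervals.
- Cachexia status is analysed with a logistic model and severity stage with an ordinal model, each at the visits where it exists.

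Holm and false-discovery-rate control are both acceptable; what matters is that the list and the method are fixed before analysis. The change affects analysis wording only, with no effect on visits, measurements or sample size. Its cost is that fewer secondary outcomes will be declared significant.

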## Materials and Methods

### Study Population

As they represent ~30% of all newly diagnosed cancers (51), this cohort study will focus on three different cancer types: breast, lung, and colorectal. The detailed inclusion and exclusion criteria are summarized in Table 1.

**Table 1 T1:** Inclusion and exclusion criteria.

**Inclusion criteria**	**Exclusion criteria**
• First-line cancer treatment	• Psychiatric, musculoskeletal, or neurological disorders
• Breast cancer, Stage II or III, treated by taxane-based CT	• Pregnant or nursing women
• Colorectal cancer, stage IV, treated by CT, RT, IT, or TT	
• Non-small cell lung cancer, stage III or IV, treated by CT, RT, IT, or TT	
• Age ≥18 years	
• Performance status WHO 0–2	
• Life expectancy >6 months	
• Ability to speak, understand and read French	
• No contraindication to physical assessments	
• Affiliate to social security system	
• Give written inform consent	

*CT, chemotherapy; IT, immunotherapy; RT, radiation therapy; TT, targeted therapy; WHO, World Health Organization performance status*.

Patients newly diagnosed with cancer by an oncologist and satisfying inclusion and exclusion criteria described in Table 1 will be informed of the study protocol. If interested, the patient will contact one of the study coordinators for full information about the study as well as to discuss any questions pertaining to it. Once the patient has provided the written consent form to participate in this study, the visits will be scheduled.

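### The three-visit mixed-design ANOVA, in its standard form, drops patients who miss only Visit 3 from the Visit 1–Visit 2 contrast too, which can understate the decline, probably more in the advanced-stage groups

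*Protocol article*

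**What the plan says.** The Statistical Analysis section fixes the repeated-measures method: "A two-way mixed-design ANOVA will be used (group [lung cancer – colorectal cancer – breast cancer] × time", where time has three levels (first, second and third visit). Pairwise differences follow if the result is significant: "a multiple-comparison analysis will be performed using an appropriate *post-hoc* test". Before this comes a multivariate step: "A multivariate analysis of variance (MANOVA) will be used on our primary outcome", taken together with all the listed secondary outcomes. The only alternative offered is "Appropriate parametric or non-parametric analyses will then be performed", and tests of normality and equal variance trigger it, not missing visits.

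The Sample Size section puts the hypothesis on the first two visits, "based on the evolution of 6-MWT distances between the first and the second visit in our study", and expects that "cancer patients will reduce, by at least 9.5%, their 6-MWT performance".

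Table 1 (Study Population) enrols different disease stages by cancer: "Breast cancer, Stage II or III, treated by taxane-based CT" against "Colorectal cancer, stage IV, treated by CT, RT, IT, or TT", with non-small cell lung cancer at stage III or IV. Under Study Design, Visit 3 falls in the week after first-line treatment is completed or at 6 months, if that comes earlier.

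**The concern.** A classical mixed-design ANOVA treats the patient's three visits as one complete row. A gap at Visit 3 removes the row, although the hypothesis needs only Visits 1 and 2. The MANOVA is stricter, since a gap in any one outcome removes the patient.

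This does harm only if the lost patients differ from those who stay, and there are two reasons to expect that they might. The Exercise Tolerance section itself says that 6-MWT distance is associated with mortality in cancer patients. The stage mix also suggests more loss in the colorectal and lung groups than in the breast group. The study aims to compare how physical status evolves across the three cancers. Selective loss that differs by cancer would shrink the decline by different amounts in each group, and part of the group × time result would then reflect who returned rather than what happened to them.

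**Working it through.** **The plan's own figure.** n = 1.96² × 62² / 7² = 301.37, which agrees with the stated 301 (three groups of 100). This is the bare formula result, with no addition for dropout.

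**Inputs from the article (Sample Size).** Baseline mean 659 m, SD 62 m, hypothesised decline 9.5%, precision 7 m. The decline in metres is 0.095 × 659 = 62.6 m.

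**Assumed inputs, not in the article.**
- Correlation between visits 0.7, so the SD of change is 62 × √(2 × (1 − 0.7)) = 48.0 m.
- The same true Visit 1–Visit 2 decline, 62.6 m, in every group.
- Probability of missing Visit 3: p(z) = 1 / (1 + exp(−(a + b·z))). Here z is the patient's Visit 1–Visit 2 decline in SD units, centred on the mean, and b is the log odds ratio per SD. The intercept is a = −2.2 for a low-loss group and −1.0 for a high-loss group.

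**Formula.** Understatement among completers = −48.0 × E[(1 − p(z))·z] / E[1 − p(z)], with z standard normal.

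| Odds ratio per SD | Loss, low / high group | Understatement, low / high (m) | Decline seen in completers, low / high (m) | Share of 62.6 m | False gap between groups (m) |
|---|---|---|---|---|---|
| 1 | 10% / 27% | 0 / 0 | 62.6 / 62.6 | 0% / 0% | 0 |
| 1.5 | 11% / 28% | 2.0 / 5.2 | 60.6 / 57.4 | 3% / 8% | 3.2 |
| 2 | 12% / 29% | 3.7 / 8.8 | 58.9 / 53.8 | 6% / 14% | 5.1 |
| 3.3 | 15% / 31% | 7.1 / 14.3 | 55.5 / 48.3 | 11% / 23% | 7.2 |

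In the last row completers show declines of 55.5 / 659 = 8.4% and 48.3 / 659 = 7.3%, against a true 9.5%. The false gap in that row is about the size of the planned 7 m precision.

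**A second set of assumptions.** With loss of 5% (breast), 20% (colorectal) and 35% (lung), an odds ratio of 2 per SD and an SD of change of 62 m, completers show 60.5, 54.3 and 49.1 m. The false breast–lung gap is 60.5 − 49.1 = 11.4 m. Averaging the Visit 1–Visit 2 change over all 100 patients per group gives 62.7, 62.1 and 62.5 m, which is the true value apart from simulation error.

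**Why a mixed model helps.** It keeps patients who have Visits 1 and 2 but not Visit 3, so their observed change still counts in the Visit 1–Visit 2 contrast. Estimates that rest on visits not attended are unbiased only if loss depends on values already observed.

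**The case against.** A reader might infer that the plan states a completers-only rule. It does not. Dropping incomplete rows is a property of the named method. The article names no analysis set and no missing-data rule, and the post-hoc test is left open. Paired Visit 1–Visit 2 tests on all available pairs, or imputation before the ANOVA, would fit the wording. A full protocol or SAP may settle this. That part of the objection stands. The model itself is fixed in the article, though, and as named it is a poor match for a two-visit hypothesis in a three-visit study.

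A reader might also infer that the decline will be understated, and unequally across cancers. The documents do not support that as a fact. They give no dropout rate, overall or by cancer, and the bias is zero when loss is unrelated to decline. Entry requires life expectancy above 6 months, WHO status 0–2 and no contraindication to the assessments, and follow-up ends at 6 months at the latest. If stopping first-line treatment early counts as completing it, progression could bring Visit 3 forward rather than cause it to be missed. These features limit loss but do not remove it.

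Larger relative figures are possible. The 7–14 m of the strongest scenario would be 24–48% of a 30 m decline. But 30 m is not the protocol's figure, and an odds ratio of 3.3 per SD is a strong mechanism.

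Finally, a mixed model is not a full answer for patients who die or cannot walk, because it extrapolates distances that were never measured and may itself understate decline. This is also a descriptive cohort, with no treatment decision resting on the test. Both points stand, and they bear on the fix and on the severity.

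**Conclusion.** The concern holds in conditional form. The named ANOVA, applied in its standard way, discards usable Visit 1 and Visit 2 data from patients who miss only Visit 3. If that loss is linked to a larger earlier decline, the analysis can understate the decline, probably more in the colorectal and lung groups than in the breast group, and can create a false group × time difference.

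At the protocol's own 62.6 m decline the understatement is about 2–7 m in a low-loss group and 5–14 m in a high-loss group, or 3–23%. It is 0 m if loss is unrelated to decline. The loss rates, the odds ratios and the 48 m SD of change are all assumptions. The difference between groups is inferred from the stage mix and not from attrition data. Should-fix, with moderate confidence.

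**What to change.** Replace the mixed-design ANOVA with a linear mixed model for repeated measures (group, visit and group × visit, unstructured covariance) fitted to every available visit. Pre-specify the Visit 1–Visit 2 contrast from this model as the test of the stated hypothesis. Add one sensitivity analysis that assumes a worse trajectory for patients who died or could not walk, because the main model does not protect against loss that depends on unobserved values.

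The cost is revised analysis wording and a little more analysis work in standard software. It needs no new data and no change to the visits, and it should be settled before the data are analysed.

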Another strength of the “global” approach of our study is the concomitant interest in CRF and cachexia, two major symptoms (81) that may have substantial interaction (5, 30–32), as suggested in the vicious cycle presented in Figure 1. CRF has been shown to promote inactivity (17, 18), leading to muscle deconditioning (19–23) mainly characterized by a loss in muscle force and mass (4). These rapid muscle alterations are in turn increasing fatigue and fueling this vicious cycle (31). The potential link between these two symptoms seems strong but requires further investigation (72). The PROTECT-01 cohort study is designed to investigate this relationship between CRF and cancer cachexia in cancer patients using repeated measures from diagnosis to the end of first-line treatment. Moreover, the combination of iso-time and iso-status measurements between the three cancers investigated (i.e., after 8 weeks of treatment and after the first-line treatment, respectively) will be important in comparing the specific maladaptation associated with the type of cancer investigated despite differences in treatment durations. The iso-time comparison will be performed to identify the rate of change for each physical and physiological parameter assessed, while the iso-status comparison will be performed to compare the consequences of first-line treatment on our series of assessments across the three cancers investigated.

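### The study promises a repeated-measures look at fatigue and cachexia, but the only association method named is a simple Pearson coefficient labelled r²

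*Protocol article*

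**What the plan says.** Rationale and Novelty in the Protocol article names the joint study of cancer-related fatigue (CRF) and cachexia as a strength, and describes the cohort as "designed to investigate this relationship between CRF and cancer cachexia in cancer patients using repeated measures from diagnosis to the end of first-line treatment".

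Statistical Analysis gives one method for relating two measurements: "interaction between specific variables will be tested with Pearson's correlation coefficients", with the coefficient labelled r². Its examples are that "we plan to test the possible correlation between subjective and objective fatigue, or between exercise tolerance/quality of life and body composition". Fatigue against cachexia is not among them, though they are offered only as examples.

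The same section provides for repeated visits and cancer groups elsewhere: "A two-way mixed-design ANOVA will be used", with group and time as factors, alongside a MANOVA across the outcomes. It also has a general sentence following the normality and variance checks: "Appropriate parametric or non-parametric analyses will then be performed".

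On the variables themselves:
- Under Questionnaires, a higher FACIT-F score means less fatigue.
- Under Body Composition and Cachexia, cachexia is a binary fat-free mass index cut-off plus a severity stage from 0 to 4, with 4 the worst. The stage is scored at the second and third visits.
- In Table 2, body composition is measured at all three visits.

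**The concern.** The question behind the repeated design is about change within a patient: does someone who loses muscle or body mass also become more fatigued? A simple Pearson coefficient takes one pair of values per row. It has no place for which patient, visit or cancer group a row belongs to. The mixed ANOVA does handle group and time, but for the mean of one outcome at a time. The MANOVA takes outcomes together but tests differences in means. Neither estimates how fatigue moves with muscle mass.

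So a declared purpose of the design falls, by default, to a method weaker than the purpose needs. Labelling the result r² adds a separate loss, because it hides whether the association runs in the expected direction. The risk is a reported fatigue–cachexia link that cannot be read as within-patient, has no sign, and may partly reflect repeated rows or differences between cancers.

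**Working it through.** The plan states no figure for this analysis. Its sample size reproduces (1.96² × 62² / 7² = 301.37, stated as 301), but it concerns 6-MWT distance and has no bearing here. Inputs from the article are three visits, "100 lung cancer patients, 100 breast cancer patients, and 100 colorectal cancer patients", and a 5% significance level. The within-patient correlations and cohort shifts below are **assumptions**; the article gives none for these variables.

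**1. Sign.** (+0.3)² = (−0.3)² = 0.09, and (+0.5)² = (−0.5)² = 0.25. If more wasting goes with more fatigue, FACIT-F should correlate negatively with cachexia stage and positively with fat-free mass. r² cannot tell either from its opposite.

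**2. If three visits were stacked.** Take two unrelated variables with the same within-patient correlation (ICC) across m visits. The variance of the naive correlation is inflated by 1 + (m − 1) × ICC². The actual error of a nominal 5% test is 2[1 − Φ(1.96/√inflation)].

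| Assumed ICC, both variables | Inflation, m = 3 | False-positive rate, formula | Simulated (300 patients, 4,000 runs) |
|---|---|---|---|
| 0.5 | 1.50 | 11.0% | 10.6% |
| 0.7 | 1.98 | 16.4% | 15.6% |
| 0.85 | 2.445 | 21.0% | 21.1% |

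With two visits, as for the 0–4 stage, the formula gives 8.0%, 10.8% and 13.5%. With one row per patient (a single visit or a change score), the rate stays at 5%.

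**3. If the three cohorts were pooled.** Let cohort means be −d, 0 and +d within-cohort SDs on both variables. The between-cohort variance is v = 2d²/3, and the pooled correlation is (r_within + v)/(1 + v).
- d = 0.25, r_within = 0: v = 0.042, pooled r = 0.04. The test at n = 300 rejects in 11% of simulated studies.
- d = 0.5, r_within = 0: v = 0.167, pooled r = 0.167/1.167 = 0.14. Rejection is 70%.
- Pooling can also mask a real association: r_within = −0.3 becomes −0.25 at d = 0.25 and −0.11 at d = 0.5.

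**4. Working within cohort instead.** For r = 0.3 at one visit with n = 100, Fisher's z gives power Φ(atanh(0.3) × √97 − 1.96) = Φ(1.09) = 86%, and a 95% CI of 0.11 to 0.47. The study is large enough to describe each cancer separately.

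**The case against.** A reader might infer that the plan stacks visits, pools the cancers and will therefore produce false-positive associations. The text supports none of this. Statistical Analysis is silent on both points. The study is organised by cancer group throughout, so correlations within group fit the text equally well, and such detail is commonly left to a statistical analysis plan. The percentages above are therefore conditional.

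Nor is it right that Pearson's method can never address the longitudinal question. Correlating change in fatigue with change in muscle mass does so with valid error control, and nothing in the article excludes it. But the article does not specify it either.

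The assumed values also deserve caution. The 0.85 in the article is the reliability of the 6-MWT, so it does not support an ICC for fatigue or muscle mass across months of treatment. Expected Impact and Perspectives sets lung and colorectal cancer together against breast cancer for cachexia, which is not the evenly spaced pattern used here, and it gives no corresponding figure for fatigue.

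On variable types, the general non-parametric sentence permits rank methods for the ordinal stage, and Pearson's r with a binary variable is the accepted point-biserial coefficient. Calling a correlation an interaction is loose wording that the following sentence corrects.

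What survives is narrower. The r² label has no sign, and the one association method named has no within-patient component although the article claims a repeated-measures investigation. Neither depends on the unstated details.

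**Conclusion.** The concern holds in this limited form: no named analysis delivers the repeated-measures study of fatigue and cachexia that Rationale and Novelty describes, and the coefficient that would stand in for it is labelled in a way that drops direction. These two points rest on the text alone.

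The size of any error depends on choices the article leaves open. It is about 11–21% false positives instead of 5% if three visits were stacked, at an assumed ICC of 0.5–0.85. It is a spurious r of 0.04–0.14, with 11–70% rejection at n = 300, if cohorts were pooled at assumed mean shifts of ±0.25 to ±0.5 SD. If correlations are run per visit or on change scores, and within cancer group, neither inflation arises.

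This is a secondary analysis, and the 6-MWT primary outcome is unaffected. The change is still worth making, because the authors present this relationship as a strength of the design.

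**What to change.** For fatigue against muscle or body-mass measures, replace the simple Pearson test with a mixed model. It should contain:
- a within-patient term (deviation from the patient's own mean, or change from Visit 1) and a separate between-patient term;
- cancer group and visit, the latter so that a shared trend over treatment is not read as an association;
- signed estimates with 95% CIs.

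A repeated-measures correlation is a simpler alternative for the within-patient part.

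For single-visit or change-score descriptions, report signed r within cancer group or adjusted for it, with its CI. Use Spearman's coefficient for the 0–4 stage, and state that it exists at Visits 2 and 3 only. Name fatigue–cachexia explicitly as one of the planned pairs.

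The data are already scheduled for collection. The cost is a revised paragraph and a little more analysis work.
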